### Objectives and aims

The Healthy Homes study has three aims: (1) estimate the effect of the Healthy Homes intervention on affordable housing residents’ voluntary adoption of smoke-free homes; (2) determine the cost of the smoke-free home intervention and determine whether it is a cost-effective use of health care resources compared to usual care; (3) using the Consolidated Framework for Intervention Research (CFIR), evaluate implementation outcomes, including characteristics of successful adopters at the individual and site levels, and the extent to which the intervention mitigates individual, interpersonal, community, and societal levels of influences of tobacco use behavior. The intervention is expected to have the primary effect of increasing the adoption of smoke-free homes, and through the mechanism of adopting a smoke-free home, it may have a secondary effect of increasing tobacco cessation (Fig 2).

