### Resident intervention

Bilingual study staff will use a language-concordant pamphlet to deliver a one-hour, one-on-one coaching session in Chinese, English, Spanish, or Vietnamese to resident participants at their housing site at the time of enrollment. This session includes the following intervention components mapped to the second level of the Behavior Change Wheel: 1) *Education* on tobacco, e-cigarette and cannabis use and exposure (secondhand and thirdhand smoke) for multigenerational households, and the personal cost of smoking; 2) *Training* on how to voluntarily adopt a smoke-free home; 3) *Restrictions* by encouraging voluntary adoption of a smoke-free home; 4) *Persuasion* using smoke-free home pledges; and 5) *Enablement* through monthly coaching interactions with lay health workers on smoking cessation (Table 1). We will observe 10% of the lay health worker and resident coaching sessions to assess the fidelity of the intervention using a checklist model and will make adjustments to the delivery of the intervention where there are substantial departures from the protocol.

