### Staff lay health worker intervention

We will deliver the housing staff intervention in English using a lay health worker model using training, education, and enablement. Lay health workers who may be bilingual in English and Spanish, Chinese, or Vietnamese will receive a two-hour training on the principles of tobacco and nicotine addiction, interactions between tobacco, e-cigarette, and cannabis use, tobacco treatment approaches, including cessation coaching and pharmacotherapy, local resources for tobacco treatment, and talking points on tobacco cessation coaching in the different languages. Through the training, lay health workers will have a chance to model the 5As (Ask, Advise, Assess, Assist, and Arrange) for smoking cessation or 2As and R (Ask, Advise, and Refer), as well as initiate conversations around tobacco use with residents [23,25]. Bilingual lay health workers will be asked to engage with residents on a monthly schedule. Lay health workers will maintain a log of these interactions, including attempts to reach participants, and will complete a monthly assessment form that includes an assessment of readiness to quit and an action plan adapted from a family-based lay health worker-led smoking cessation intervention (31). The action plan will include prompts to (1) talk to family or friends, (2) make some changes towards smoke-free home adoption or smoking cessation, (3) call the Kick It California telephone quitline, and (4) talk to their healthcare provider or neighborhood pharmacy (if they do not have a healthcare provider) for cessation coaching. Because residents’ encounters with lay health workers will occur as part of routine care, we will request permission from a sample of staff and resident dyads (n = 40) to observe and record these interactions using a standardized evaluation form to assess fidelity.

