### Control

Resident and staff participants in the wait-list control group will receive usual care, which involves no on-site treatment for smoking cessation or smoke-free home adoption.

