*Mental health.* We will screen for depression using the 10-item Center for Epidemiologic Studies Depression Scale [55], anxiety using a seven-item anxiety scale (Generalized Anxiety Disorder-7) [56], and post-traumatic stress disorder (PTSD) using the Primary Care PTSD Screen [57].

*Alcohol and substance use disorders.* We will ask participants about lifetime use of opioids, methamphetamines, crack/cocaine, and cannabis, and for those who report lifetime use, we will ask about use in the past 30 days and number of days used in the past 30 days. To assess cannabis use, we will administer the Cannabis Use Disorders Identification Test-Revised (CUDIT-R) [58]. To assess risky alcohol use, we will administer the Alcohol Use Disorders Identification Test (AUDIT-C) [59,60].

*Satisfaction and usefulness of the intervention* For intervention recipients, at 3- and 6-month follow-ups, we will evaluate satisfaction with the intervention using questions with Likert responses and usefulness using a previously validated item, ‘In the past three months, what role did the intervention play in helping you quit smoking?’

*Exposure to lay health worker coaching* At the 3- and 6-month follow-ups, we will ask residents whether they had any coaching encounters with lay health workers, the number of these encounters, whether they were asked and advised to quit by lay health workers, and the satisfaction and usefulness of these encounters.

*Evaluating the potential for cross-contamination* At the 3- and 6-month follow-ups, we will ask participants who received the intervention whether they had discussed the intervention or shared materials with family and neighbors in their building.

*Cost data.* We will collect data on costs through publically available data (e.g., average sales price of cigarettes, CPT code for cessation services and cost, average time for cessation services) and study business ledger (e.g., intervention start-up material cost, training cost). We will collect and analyze lay health worker time use in the intervention through a time and motion study [61].

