We will conduct several secondary analyses. First, we will fit a generalized mixed-effects logistic model of the secondary outcome, point prevalence abstinence, similarly to the primary analysis. Second, participants lost to follow-up will be compared to those who completed the study to assess whether there are systematic differences in baseline covariates between the two groups. Third, we will include sex, race/ethnicity, and their interactions with the group and time in the logistic mixed effects model to examine any sex and/or race/ethnicity differences in the intervention effects on the outcomes. Fourth, we will perform mediation analyses to identify the mechanisms/pathways by which the intervention may have impacted smoke-free home adoption or point prevalence abstinence outcomes, including knowledge and skills to adopt a smoke-free home, change in smoke-free policy attitudes, exposure to lay health workers, neighborhood environment, and fidelity of intervention delivery. Fifth, we will explore the moderation effects of children or pets at home, indoor cannabis use, or other combustible tobacco use on intervention outcomes of smoke-free homes and point prevalence abstinence outcomes via mixed effects regression models. Replicability of within-group changes on primary and secondary outcomes will be tested by comparing baseline to 6-month changes in the intervention group to corresponding 6- to 12-month changes in the waitlist control group.

Analyses of lay health worker data will include a pre-post training analysis of the smoking knowledge, attitudes, practices, efficacy, and barriers scales (SKAP) using generalized mixed linear models. We will fit generalized mixed linear regression models to examine factors associated with a change in each of the scales, accounting for correlations due to clustering by sites and residents and adjusting for demographics, geographic location, lay health worker smoking status, coaching encounters with residents, and lay health worker job role.

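### Delivery fidelity is listed as a mediator although it has no value in the control arm, and the named mediators do not include the smoke-free home as the route to cessation

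*Protocol article*

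**What the plan says.** The Protocol article, under Statistical analyses, plans mediation analyses as the fourth of its secondary analyses. Their purpose is to identify the "mechanisms/pathways by which the intervention may have impacted smoke-free home adoption or point prevalence abstinence outcomes". Five candidates are named, "including knowledge and skills to adopt a smoke-free home, change in smoke-free policy attitudes" and then "exposure to lay health workers, neighborhood environment, and fidelity of intervention delivery". Smoke-free home adoption appears in that sentence only as an outcome.

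Four other places bear on the list:

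- **Objectives and aims** states how cessation is expected to come about: "through the mechanism of adopting a smoke-free home, it may have a secondary effect of increasing tobacco cessation".
- **Control** describes the comparator as "usual care, which involves no on-site treatment for smoking cessation or smoke-free home adoption".
- **Resident intervention** says how fidelity is measured: "We will observe 10% of the lay health worker and resident coaching sessions to assess the fidelity of the intervention". **Staff lay health worker intervention** adds "a sample of staff and resident dyads (n = 40) to observe and record these interactions".
- **Resident questionnaire measures** covers lay health worker exposure at the 3- and 6-month visits: "we will ask residents whether they had any coaching encounters with lay health workers, the number of these encounters".

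**The concern.** A mediator in a two-arm comparison needs a value in both arms, because the first link in the chain is the effect of assignment on the mediator. Fidelity describes how well something was delivered. Where nothing is delivered it is not low or zero; it does not exist. An analyst who follows the text literally must drop the control arm, which removes the randomised contrast, or assign controls an arbitrary value, which makes the result depend on that choice.

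The second issue is one of priority. The article states one mechanism for its secondary outcome: residents make the home smoke-free, and quitting follows. If the pathways named in advance leave that one out, the trial could report indirect effects through other variables without having committed to test its own hypothesis about cessation.

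**Working it through.** The article gives no power or precision figure for mediation, so there is nothing of its own to reproduce. The check sets the sections side by side and adds simple counts.

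**1. Can an indirect effect through fidelity be defined?** Write A for arm (1 intervention, 0 control), M for the mediator and Y for the outcome. The indirect effect is E[Y(1, M(1))] − E[Y(1, M(0))]. M(0) is the fidelity a resident would have had under usual care. The Control section says there is no on-site treatment, so M(0) has no value and the second term is undefined.

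**2. Does coding controls as zero rescue it?** In a model of Y on A and M with M = 0 for all controls, M does not vary among controls. The slope of Y on M then comes only from intervention residents. The arm-to-mediator effect is the mean fidelity score in the intervention arm. Their product is a non-randomised within-arm slope multiplied by the distance from the observed mean to an arbitrary zero on the checklist. Change the zero point of the scale and the indirect effect changes.

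**3. How many residents would have a fidelity value?** Planned residents are 272 per arm (Resident participants).

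- Controls: 0 of 272 during the 6-month comparison. Controls who take up the intervention do so after their 6-month visit (Study design), too late for that contrast.
- Coaching sessions, assuming one session per resident: 0.10 × 272 = 27.2, about 27.
- Dyads: 40, and 40/272 = 14.7%, assuming each involves a different intervention resident.
- If the two samples do not overlap: 27 + 40 = 67, and 67/272 = 24.6%.
- The 10% could also be read as covering the monthly lay health worker sessions. Assuming six monthly contacts plus the initial session, all held, there are 7 × 272 = 1,904 sessions, of which 10% is 190. These would reach at most 190 residents, and fewer if anyone is observed twice.

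The intervention-arm count therefore depends on how the sampling is read. The control count of zero does not, and it settles the point.

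**4. Is the stated cessation pathway among the named mediators?** The five named are knowledge and skills, policy attitudes, lay health worker exposure, neighborhood environment and fidelity. The mechanism in Objectives and aims is intervention → smoke-free home → cessation, and its middle term is not one of the five.

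**5. Are the data for that pathway planned?** Yes. Smoke-free home adoption is in the resident questionnaire, data are collected from all participants at baseline, 3 and 6 months (Study timeline and follow-up), and CO-verified abstinence is a 6-month outcome. A 3-month mediator can therefore be placed before a 6-month outcome.

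**The case against.** The strongest reply has four parts.

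*The list is open and a figure is missing.* The mediators are introduced as examples, and Fig 2, captioned as covering mediators, moderators and outcomes, is not shown. A condensed article may also leave the full mediator model to the analysis plan. This stands. A reader might infer that the trial leaves its own mechanism untested, and the document does not support that. It supports only that the analysis text does not name it.

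*Lay health worker exposure can be a mediator.* A reader might infer that it is simply arm under another name. It is measured after randomization, asked of residents with no stated restriction by arm, and changed by assignment. It should also vary within the intervention arm: 30–50 trained staff are expected for 48 sites, and their logs record attempts to reach participants. The main coaching session is given separately by study staff, so exposure is not identical to assignment. This stands. What remains is a matter of interpretation: monthly coaching is itself a component of the intervention and is expected to be near zero in controls, so any indirect effect leans on non-randomised differences in dose.

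*Neighborhood environment is not ruled out.* Distances to retailers are unlikely to move in response to coaching. But Aim 3 speaks of mitigating community-level influences, and neighborhood safety is among the resident questionnaire measures; residents' perception of it could change. The objection is one of plausibility, so saying that three of the five named mediators are unusable would go too far.

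*This is a secondary analysis.* True, and it limits the weight of the point.

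None of this helps fidelity. The text names it explicitly, and no later specification can give it a value under usual care.

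**Conclusion.** The point holds in a limited form. One of the five named mediators, fidelity, cannot be analysed as the text says: it has no value for any of the 272 controls and is observed in only part of the intervention arm (about 27 to 67 of 272 if the 10% means one session per resident, more if monthly sessions count). This rests only on the description of usual care and on how fidelity is sampled.

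The named list also does not state the smoke-free home as mediator of abstinence. That is an improvement worth making rather than a proven omission, given the open list and the figure not shown. Lay health worker exposure may stay if it is read as a treatment component or dose. Treating neighborhood environment as a moderator is a suggestion, not the correction of an error.

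The primary intention-to-treat contrast, the secondary outcome model and the sample size of 544 are untouched.

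**What to change.** In the fourth secondary analysis under Statistical analyses:

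1. Remove fidelity from the mediators. Analyse its association with outcomes within the intervention arm, in the observed subsample, and label it non-randomised.
2. Name smoke-free home status at 3 months as mediator of CO-verified abstinence at 6 months. Say how 3-month status is defined: three months is about 90 days, so the 90-day threshold of the primary outcome would count almost only residents who adopted at enrollment. Acknowledge that a resident who has already quit by 3 months will also tend to report a smoke-free home.
3. Keep lay health worker exposure if wanted, with a sentence saying that it is a treatment component or dose expected to be near zero in controls.
4. Optionally, move neighborhood environment to the moderators in the fifth secondary analysis.

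The cost is wording only: fidelity observation, the 3-month questionnaire and the 6-month CO test are already planned. Recruitment was still open at submission and data collection is expected to run to the end of 2026, so the change can be made before results are known. The downside is that the within-arm fidelity results carry no causal claim.

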## Methods

### Study design

We will conduct a wait-list cluster randomized controlled trial in which housing sites will be randomized to intervention and wait-list control groups [25,32,33]. Participants in the intervention sites will receive the intervention first. Those in the wait-list control sites will receive usual care for the first 6 months and then be offered the choice to receive the intervention after they complete their 6-month follow-up visit; those in the wait-list control group who choose to receive the intervention will be observed for an additional 6 months. This study was approved by the University of California, San Francisco Protocol Review and Monitoring Committee (Institutional Review Board number: 23–39015).

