### Study timeline and follow-up

The study duration for intervention group participants is 6 months from the time of enrollment. Wait-list control group participants (i.e., both residents and staff) will be offered the intervention after the intervention group participants within the same cluster receive their intervention; participants who choose to receive the intervention will be observed for an additional 6 months. Data will be collected for all participants at baseline (pre-intervention), 3 months, and 6 months; for the control cross-over set of participants, data will also be collected at 9 and 12 months (i.e., 3- and 6-months post-intervention) (Fig 1).

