#### Lay health worker outcome.

The primary outcome of interest for lay health worker staff is a change in SKAP score from baseline to the 6-month follow-up.

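### The staff primary outcome (SKAP change) is given only a pre-post analysis without a randomised-group term, although untrained wait-list staff are measured at the same visits; residents are also named as a clustering level for a staff score

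*Protocol article*

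**What the plan says.** The Lay health worker outcome section states: "The primary outcome of interest for lay health worker staff is a change in SKAP score from baseline to the 6-month follow-up". The Statistical analyses section then gives two staff analyses. The first: "Analyses of lay health worker data will include a pre-post training analysis of the smoking knowledge, attitudes, practices, efficacy, and barriers scales (SKAP", fitted with generalized mixed linear models. The second is a set of models of factors associated with change in each scale. Their treatment of clustering is described as "accounting for correlations due to clustering by sites and residents". Their covariates are set out in these words: "adjusting for demographics, geographic location, lay health worker smoking status, coaching encounters with residents, and lay health worker job role". Randomised group appears in neither analysis.

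The design sections describe a staff comparison group. Under Study design, "housing sites will be randomized to intervention and wait-list control groups", and wait-list sites have usual care for the first 6 months. Under Control, "Resident and staff participants in the wait-list control group will receive usual care". Under Study timeline and follow-up, "Wait-list control group participants (i.e., both residents and staff) will be offered the intervention after" the intervention group has had it, and the 9- and 12-month visits of those who cross over are labelled 3 and 6 months post-intervention. The same section says: "Data will be collected for all participants at baseline (pre-intervention), 3 months, and 6 months". The Lay health worker questionnaire measures section puts SKAP at those three visits.

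For residents, by contrast, the Statistical analyses section specifies group, time and their interaction, with a group contrast at 6 months.

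**The concern.** The baseline-to-6-month window that defines the staff outcome is the window in which wait-list staff are untrained. A before-after comparison cannot separate training from anything else that moves SKAP over 6 months, such as having answered the survey before, or wider change in attitudes to smoking in the housing sector. If both arms share such a shift, an arm contrast removes it and a pre-post analysis reports it as training.

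The plan also leaves the role of wait-list staff unclear. Their baseline-to-6-month change precedes any training. Their 6- to 12-month change follows training but lies outside the window that defines the outcome.

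Separately, SKAP is measured on the staff member, who works within a site. Residents are a level of the resident data, and the phrase looks carried over from that model. One listed adjustment variable, coaching encounters, arises after training and so should not be in an estimate of the training effect.

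**Working it through.** The article states no power, effect size or SD for SKAP, so there is no staff figure to reproduce. What follows is an illustration.

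**Inputs**
- From the article: 30 to 50 staff (Staff participants), no split by arm.
- From the article, but not stated for staff: 75% retention (Retention; Power and sample size) and two-sided alpha of 0.05 (Power and sample size, resident outcomes).
- Assumed: equal arms, 75% retention applied to staff, correlation r between baseline and 6-month SKAP of 0.5 to 0.7, no site clustering, normal approximation.
- Analysed per arm: 30/2 × 0.75 = 11.25 and 50/2 × 0.75 = 18.75. Both arms pooled: 22.5 and 37.5.

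**Formulas, in SD units of SKAP**
- Smallest observed pre-post change that is significant: 1.96 × √(2(1 − r)/n).
- Arm difference detectable at 80% power, adjusted for baseline, m per arm: 2.8 × √((2/m)(1 − r²)).

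| Quantity | n or m | r = 0.5 | r = 0.7 |
|---|---|---|---|
| Pre-post threshold, trained arm, 30 enrolled | 11.25 | 0.58 | 0.45 |
| Pre-post threshold, trained arm, 50 enrolled | 18.75 | 0.45 | 0.35 |
| Pre-post threshold, both arms pooled, 30 enrolled | 22.5 | 0.41 | 0.32 |
| Pre-post threshold, both arms pooled, 50 enrolled | 37.5 | 0.32 | 0.25 |
| Arm contrast at 80% power, 30 enrolled | 11.25 per arm | 1.02 | 0.84 |
| Arm contrast at 80% power, 50 enrolled | 18.75 per arm | 0.79 | 0.65 |

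The extremes: 1.96 × √(0.6/37.5) = 0.25 and 1.96 × √(1/11.25) = 0.58; 2.8 × √(0.1067 × 0.51) = 0.65 and 2.8 × √(0.1778 × 0.75) = 1.02. The two kinds of row answer different questions: the first four are significance thresholds, the last two are effects detectable at 80% power. With 2.8 in place of 1.96 the pre-post range would be 0.35 to 0.83 SD.

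**How often drift alone would be called an effect.** Suppose training does nothing and SKAP drifts by s. With SE = √(2(1 − r)/n), the rejection probability is 1 − Φ(1.96 − s/SE) + Φ(−1.96 − s/SE). Take s from 0.2 to 0.5 SD (assumed) and full retention:
- 15 trained staff analysed: 12% (s = 0.2, r = 0.5) to 71% (s = 0.5, r = 0.7).
- 25 trained staff analysed: 17% to 90%.

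The arm contrast stays at about 5%, because a shift common to both arms cancels.

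**Price of the contrast.** For change scores without clustering, the arm contrast has variance 2 × 2(1 − r)/(N/2), against 2(1 − r)/N for a pre-post test pooling all N staff. The ratio is 4, so the detectable difference doubles.

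**The case against.** **An arm comparison may still be planned.** The article says what the staff analyses will include, which is not exclusive, and an analysis plan not shown may add a contrast. A reader might infer that randomisation has been abandoned for staff; the text does not establish that. What stands is that the only analyses named for this outcome have no group term, while the resident model in the same section has one.

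**The standard errors are not shown to be wrong.** A reader might infer this from the absence of a worker-level random effect. The clustering phrase belongs to the factors-of-change models. With one change score per worker, no worker effect is needed there. For the pre-post mixed model the random effects are not listed, which a condensed article may leave to its analysis plan. The standard errors would be wrong only if repeated scores were modelled without a worker effect. What remains is that residents are not a level of these data.

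**The arm contrast has limits of its own.** Sites are randomised, not staff. Staff volunteer after email or in-person invitation, and the article does not say that they enrol before allocation is known. Selective turnover can bias an arm contrast too. With 30/48 = 0.6 to 50/48 = 1.0 staff per site, some sites may contribute nobody and a site effect may be weakly identified. The staff number is also described as those enrolled to receive training, so the size of the untrained group by 6 months is uncertain. These points limit precision and call for a stated limitation; they do not make the uncontrolled comparison better.

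**The stake is limited.** None of the three aims is a staff training effect, and nothing is powered on SKAP. The trial's main resident inference is untouched. This is right, and it sets the weight of the point.

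**Conclusion.** The point holds for the analysis as stated. The staff primary outcome is given a pre-post analysis and a factors-of-change analysis, neither with the randomised group, although a concurrent site-randomised group is untrained and measured throughout the same 6 months. Naming residents as a clustering level is a wording error in the factors-of-change models.

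Under the stated assumptions, an observed change of about 0.25 to 0.58 SD is enough for pre-post significance (0.35 to 0.58 SD if only the trained arm is analysed), against an arm contrast that detects about 0.65 to 1.0 SD at 80% power. The documents give no evidence on how large any SKAP drift would be, so these figures show vulnerability, not a predicted bias. Site clustering, where a site has more than one staff member, would raise the arm-contrast figures. The change should be made before analysis, but it does not threaten the trial's main conclusion.

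**What to change.** - Make the between-arm difference in 6-month SKAP score, adjusted for baseline SKAP, the main staff analysis, with a random effect for site. If 3-month scores are included, add a random effect for staff member.
- Do not adjust this estimate for coaching encounters.
- Replace residents with staff member in the clustering statement. Where a single change score per worker is modelled, the staff level drops out and site alone remains.
- Keep the pre-post change as descriptive, and say which window wait-list staff contribute to it.
- Report that staff volunteered within randomised sites, as a limitation of the contrast.

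The cost is analysis-plan wording. The data are already scheduled, and by the Current status section collection runs to 31 December 2026. The downside is a wider interval, which at this sample size may well be inconclusive.
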